### 3.1 Definitions

Baseline is defined as all measurements taken within the week before administration of the first intervention.

Intervention is defined as the administration of verum (Yakult) or placebo.

Verum is defined as one bottle of Yakult containing a minimum of  $6.5 \times 10^9$  *Lactobacillus casei* Shirota once a day during a course of antibiotics and for 7 days after the course finishes.

Placebo is defined as a drink with identical taste and appearance to the test intervention but not containing any bacteria (including *Lactobacillus casei* Shirota), once a day during a course of antibiotics and for 7 days after the course finishes.

Study start point is defined as the first day of administration of the first intervention.

Study endpoint is defined as the last day following 30 days of follow-up after finishing administration of the intervention.

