### **5.3 Informed consent procedure**

The study team will be contacted by the ward and informed when a patient is to start / or has been started on antibiotic therapy for an infection. A member of the research team will approach the subject and provide the participant information sheet and if the subject shows an initial interest, the study coordinator will explain (1) the purpose of the study, (2) the procedures, (3) the risk / benefits, (4) alternatives to participation, (5) and the confidentiality. At this stage, the study coordinator will emphasise that the current feasibility study does not influence the provision of other healthcare services delivered by the specialised services. Candidate will be offered up to 24 hours to consider participation in the current study and will have the opportunity to ask any study-related questions that arise. Should the patient wish to go ahead with the study, consent will be specifically sought for 1. participation in this study and 2. the use and storage of de-identified data for the current research project.

Patients able to consent for themselves will be asked to sign an informed consent form. A witness will be asked to sign on behalf of those patients unable to sign the form due to physical disabilities. After obtaining informed consent, patients will be allocated (SM xx, Os xx, or Ts xx depending on sites), undergo their baseline assessments and offered Yakult or placebo (according to randomisation result) within 48 hours of commencing their antibiotic. The study drink will then be given once a day at the drug round in accordance with the protocol.

A master ID log will be maintained at each site.

The participant will be informed about their right to withdraw from the study at any time and for any reason without sanction, penalty, or loss of benefits to which the patient is otherwise entitled. A register will be kept of all patients who withdraw from the study. The reason for consent withdrawal will be documented along with the following core patient characteristics: age, gender and level and severity of spinal cord injury.

A copy of the signed Informed Consent Form - approved by the Research Ethics Committee - will be retained at the investigational site along with other investigational forms. A copy of the signed informed consent form will be placed into the patient's medical record, patient file (original) and a copy will be handed over to the patient.

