#### 5.5.2 Study procedure: opening assessments

After having obtained informed consent (1x copy to patients; 1x copy in medical notes; 1 x original in the investigator site file), basic patient's clinical characteristics and baseline measurements, as outlined on the Case Report Form (CRF, see [Item 12.1](#)), will be collected. No intervention will be administered prior to the completion of the study opening visit.

- Baseline demographics and clinical data
- Record use of medications (including use of antibiotics, laxatives, anti-diarrhoeal agents, proton pump inhibitors, H2 blocker)
- Nutrition risk scores – Spinal Nutrition Screening Tool (Wong et al, 2010, 2012)

- Quality of Life evaluation – WHO-QoL BREF ([http://www.who.int/substance\\_abuse/research\\_tools/en/english\\_whoqol.pdf](http://www.who.int/substance_abuse/research_tools/en/english_whoqol.pdf))
- Bowels function measures – stool type, duration of diarrhoea  
Definition of diarrhoea: two or more loose stools, Bristol Stool Scale (O'Donnell LD, 1990) type 5 or above.  
Constipation: using Rome III criteria: Functional constipation ([http://www.romecriteria.org/assets/pdf/19\\_RomeIII\\_apA\\_885-898.pdf](http://www.romecriteria.org/assets/pdf/19_RomeIII_apA_885-898.pdf)) (Drossman DA, 2006).
- Stool Specimen analysis (Kubota *et al.* 2014)  
One sample will be taken, frozen and stored frozen and then sent to YHER for TaqMan PCR analysis of toxigenic *C. difficile*. This analysis will be dependent on available resources at YHER. Further microbial analysis may also be done. This will be in the participant information sheet and on the consent form.

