#### **5.5.6 End of Intervention; Start of Follow-up**

An episode of diarrhoea will be defined as two or more liquid stools (Bristol Stool Scale types 5, 6 and 7) that is greater than normal for the inpatient over a 24 hour period.

The frequency and duration of diarrhoea / constipation will be monitored.

Patients' quality of life (WHO-QoL: *Spinal Cord* 48:762-769; *Spinal Cord* 50:112-118), medication charts (especially antibiotics, laxatives, anti-diarrhoeal agents, proton pump inhibitors and H2 blocker) and nutrition risk scores (Wong *et al.*, 2012) will be assessed **at baseline (within 24 hours of starting intervention, Yakult/placebo), 7 +/- 3 days after finishing course of antibiotics and at follow up (30 +/- 3 days after finishing course of antibiotics).**

Duration of hospital stay will be recorded on the patient's hospital record.

Bowel function will also be monitored throughout (i.e. stool type; duration of diarrhoea / constipation relapse).

In addition, faecal samples will be routinely acquired at in the event of diarrhoea, and at the end of intervention. These samples will be frozen and stored, before sending to YHER for microbiological analysis, including TaqMan PCR analysis of toxigenic *C. difficile*. Technique will be based on the paper by Kubota *et al.* (2014).

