### **Transport of stool specimen to YHER**

Citysprint couriers will be used to courier samples to YHER. Contact details: [name] (Clinical Trials Co-Ordinator, [contact]). Samples will not have any patient identifiable information (with a study project number).

The PI will have a date code and/or additional code to indicate the different samples as follows:

**Routine sample #1 (baseline)** = collected at baseline within 24 hours of starting intervention (Yakult/placebo). The patient will only just have started antibiotics and intervention (i.e. Yakult or placebo). **Data code: 2 X X X**

**Routine sample #2 (ABx+7d)** = collected seven days after the patient stops antibiotics (with a window of  $\pm 3$  days), and thus on the day they stop intervention (Yakult/placebo). **Data code: 3 X X X**

**Routine sample #3 (ABx+30d)** = collected 30 days after the patients stops antibiotics (with a window of  $\pm 3$  days), and thus 23 $\pm 3$  days after they stop intervention (Yakult/placebo). **Data code: 4 X X X**

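### The baseline stool sample must precede the first study drink in sections 3.1 and 5.5.2, but section 5.5.8 describes it as taken once the drink has started, so the secondary stool-change endpoints can rest on a post-treatment baseline

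*Protocol*

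**What the plan says.** **Baseline before the first drink**

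- Section 3.1: "Baseline is defined as all measurements taken within the week before administration of the first intervention".
- Section 5.5.2: "No intervention will be administered prior to the completion of the study opening visit". The assessments listed there include the WHO quality-of-life questionnaire, the nutrition risk score and one stool sample.
- Section 5.3 gives the same order: after consent, patients "undergo their baseline assessments and offered Yakult or placebo".
- Section 5.5.3 releases the randomisation list to the product distributor only after the opening assessment is done.
- Appendix 2 puts nutrition score, quality of life and stool collection in the opening-visit column, ahead of the allocation column.

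**Baseline tied to the start of the drink**

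- Section 5.5.8 (transport of stool specimens), routine sample #1: "collected at baseline within 24 hours of starting intervention (Yakult/placebo", followed by "The patient will only just have started antibiotics and intervention (i.e. Yakult or placebo".
- Section 5.5.5 attaches the 24-hour window to the faecal samples. Quality of life, medication charts and nutrition score are there simply assessed at baseline.
- Sections 5.5.6 and 5.5.7 attach the window to quality of life, medication charts and nutrition score: "at baseline (within 24 hours of starting intervention, Yakult/placebo".

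**The concern.** The timing of a baseline sample is an instruction to the people who collect it. Section 5.5.8 gives that job to ward nurses, at three centres, and the protocol hands them two different rules. A stool collected at the wrong time cannot be put right in the analysis.

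Routine sample #1 is the reference point for two secondary endpoints: change in *C. difficile* toxin-gene prevalence (6.2.3) and change in gut microbiota (6.2.4). By sections 3.1 and 5.4 the active bottle contains at least 6.5 × 10^9 live LcS and the placebo contains none. If the first bottle alters what is measured in the stool, it does so in one arm only, and part of the treatment effect is then built into the baseline. For any continuous microbiota measure, the ANCOVA in section 7.4 would also be adjusting for a value taken after treatment began.

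**Working it through.** **1. Can the passages be read together?**

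| Section | What it covers | Timing relative to the first drink |
|---|---|---|
| 3.1 | all baseline measurements | before |
| 5.5.2 | opening visit, including stool | before |
| 5.3 | baseline assessments | before |
| 5.5.5 | faecal sample | within 24 hours, direction not given |
| 5.5.6, 5.5.7 | quality of life, medication charts, nutrition score | within 24 hours, direction not given |
| 5.5.8 | routine stool sample #1 | within 24 hours, drink already started |

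An assessment made in the 24 hours before the first drink satisfies 3.1, 5.5.2 and 5.5.5 to 5.5.7 together. It does not satisfy 5.5.8, which describes a patient who has begun the drink. The contradiction is therefore strict for stool sample #1. For the other measurements it is only an ambiguity, which 5.3, 5.5.2, 5.5.3 and Appendix 2 resolve in favour of before.

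**2. Which analyses use the stool baseline?**

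- Primary endpoint: occurrence of AAD, compared by Fisher's exact and χ² tests (7.4). No baseline value enters.
- Sample size (7.2): 56.3% against 38.4% with two-sided α = 0.05 (sidedness assumed), 90% power and pooled variance gives 162 per group, and 162 / (1 − 0.10) = 180 per arm. Both figures reproduce, and neither depends on the baseline definition.
- Toxin-gene prevalence: uses sample #1, but that sample is tested only if prevalence in sample #3 is at least 2% (5.5.8). It is a proportion, so the ANCOVA for continuous outcomes does not apply.
- Gut microbiota: uses sample #1 if the optional further analysis is done (6.2.4).

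**3. How large could the distortion be?**

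The protocol gives no figure, so what follows is illustration under assumptions. Let *f* be the share of the final treatment effect already present in the baseline stool, and *b* the ANCOVA slope on baseline.

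- Share of the effect kept by a change score: 1 − *f*
- Share of the effect kept by ANCOVA: 1 − *b* × *f*

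| *f* | Change score | ANCOVA, *b* = 0.3 | ANCOVA, *b* = 0.7 |
|---|---|---|---|
| 0 | 100% | 100% | 100% |
| 0.05 | 95% | 98.5% | 96.5% |
| 0.25 | 75% | 92.5% | 82.5% |

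If the early shift ran against the final effect, *f* would be negative and the effect would be exaggerated: at *f* = −0.25 a change score shows 1 + 0.25 = 125%. Neither the size nor the sign of *f* can be taken from the protocol.

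**The case against.** The strongest reply is that the protocol already fixes the order. Sections 5.3, 5.5.2 and 5.5.3 and Appendix 2 all put the opening assessments before the drink, and a window stated as within 24 hours of starting can mean the 24 hours before. That answers the matter for quality of life and nutrition score. A reader might infer from 5.5.6 and 5.5.7 that the ANCOVA baselines for those scores are also post-treatment. The documents do not support this: the wording at most leaves it open, and other sections close it. The reply fails for stool sample #1, because 5.5.8 states the direction.

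It is also fair to say that the exposed endpoints are conditional: the toxin-gene PCR may cover only a subset of samples, and the microbiota work may not be done. That lowers the weight of the point but does not remove the conflict.

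Two further inferences go too far.

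- **Bias toward zero.** This needs the stool to change soon after the first drink, and in the same direction as the final effect. The protocol supports neither.
- **A baseline up to 72 hours late.** Adding the 48 hours allowed from first antibiotic dose to first drink to the 24-hour window gives 48 + 24 = 72 hours. Up to 48 of these hours are antibiotic exposure before the drink. That exposure arises in both arms under randomisation and would remain with a fully pre-drink baseline. Only the 24 hours after the drink bear on this point.

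Finally, how to analyse late samples can be left to a statistical analysis plan. When to collect the sample cannot, because the protocol states that rule itself and states it in two ways.

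**Conclusion.** The point holds for the baseline stool sample. Sections 3.1 and 5.5.2 require it before the first drink, and 5.5.8 describes it as taken after. A site following 5.5.8 can produce a post-treatment baseline for change in toxin-gene prevalence and change in gut microbiota, with live LcS given in one arm only. The resulting distortion may be nil and cannot be estimated from the protocol; the percentages above rest wholly on assumed values of *f* and *b*. The primary analysis and the sample size are unaffected, and quality of life and nutrition score are adequately protected by other sections. This is an internal inconsistency of modest weight, confined to conditional secondary laboratory endpoints. It is worth correcting because a mistimed sample cannot be recovered.

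**What to change.** - **Section 5.5.8:** define routine sample #1 as a stool passed before the first study drink, and remove the description of the patient as having already started it.
- **Sections 5.5.5 to 5.5.7:** state that the baseline window lies before the first drink.
- **If no pre-drink stool is available:** accept the first stool within 24 hours of the first drink, record the clock times of drink and stool, and flag the sample. The start of the drink need not wait for a stool.
- **Analysis:** repeat the stool-change analyses without flagged samples.

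The cost is a few words in four sections, two time fields and a flag on the case report form, and one sensitivity analysis. The downside is that some participants will have only a flagged baseline stool. The time available is short: the drink must start within 48 hours of the first antibiotic dose, and section 5.3 offers patients up to 24 hours of that to decide. If all 24 are used from the first dose, 48 − 24 = 24 hours remain. Section 5.5.5 also limits sample collection to weekdays. The sensitivity analysis will therefore have fewer participants, and the number of flagged samples should be reported by arm.

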## 4 Primary and secondary objectives

### 4.1 Primary Objective

To assess the efficacy of a probiotic preparation (Yakult) containing a minimum of  $6.5 \times 10^9$  *Lactobacillus casei* Shirota (LcS) compared to placebo for the prevention of antibiotic-associated diarrhoea (AAD).

### 4.2 Secondary Objectives

To analyse the effect of LcS on the

- Occurrence of *C. difficile* diarrhoea (CDAD)
- Duration of diarrhoea
- Change in gastrointestinal microbiota (stool specimen analysis)
- Quality of life

- To determine if malnutrition (undernutrition) is a risk factor for AAD and CDAD
- To determine if use of proton pump inhibitors (PPI) is a risk factor for AAD and CDAD.

## 5 Trial design

This is a multicentre, randomised, double-blind, placebo-controlled, parallel trial to be conducted in three specialised Spinal Cord Injury Centres in the United Kingdom. See Appendix 5 for the decision tree outlining recruitment and randomisation of subjects.

### 5.1 Study population

#### 5.1.1 General Inclusion Criteria

- Adult ( $\geq 18$  years)
- Patient is likely to remain in the SCI centre for more than 6 weeks can be included
- Newly started antibiotics (the course of antibiotics used as treatment for an infection should be a minimum of 3 days) (single or multiple)
- Able to take study drinks within 48 hours of first dose of antibiotics

#### 5.1.2 General Exclusion Criteria

- Re-recruit patient (ie, only patients recruited for the first time are allowed)
- Antibiotic use in the 30 days prior to the study product first administration apart from a single dose of prophylactic given more than 14 days before the study product's first administration.
- Diarrhoea within the preceding 7 days prior to commencement of intervention
- Bowel pathology that could result in diarrhoea
- Recent bowel surgery
- Infective endocarditis
- Active inflammatory bowel disease
- Pancreatitis
- Regular probiotic use
- Any illness requiring ITU intervention or systemic sepsis
- Immunosuppression
- Nil-by-mouth status for any reason
- Non-functioning gut (Include those on Parenteral Nutrition)
- Known cows' milk protein intolerance
- Psychiatric or cognitive conditions that may interfere with the study
- Patients incapable of providing informed consent due to a mental incapacity
- Patients unlikely to comply with study requirements
- Pregnant or breastfeeding women
- Prisoners

### 5.2 Recruitment of participants / Screening

An invitation letter from potential participant's consultant and a participant information sheet will be sent to all patients with SCI admitted to the SCI centre upon admission. A member of study team will be available to answer any study queries upon request.

All admitted patients reviewed for potential consideration for the study and which are excluded, will be logged on the pre-screening log maintained by the study team.

Further details on the general process for obtaining informed consent can be found under **Item 5.3**.

### **5.3 Informed consent procedure**

The study team will be contacted by the ward and informed when a patient is to start / or has been started on antibiotic therapy for an infection. A member of the research team will approach the subject and provide the participant information sheet and if the subject shows an initial interest, the study coordinator will explain (1) the purpose of the study, (2) the procedures, (3) the risk / benefits, (4) alternatives to participation, (5) and the confidentiality. At this stage, the study coordinator will emphasise that the current feasibility study does not influence the provision of other healthcare services delivered by the specialised services. Candidate will be offered up to 24 hours to consider participation in the current study and will have the opportunity to ask any study-related questions that arise. Should the patient wish to go ahead with the study, consent will be specifically sought for 1. participation in this study and 2. the use and storage of de-identified data for the current research project.

Patients able to consent for themselves will be asked to sign an informed consent form. A witness will be asked to sign on behalf of those patients unable to sign the form due to physical disabilities. After obtaining informed consent, patients will be allocated (SM xx, Os xx, or Ts xx depending on sites), undergo their baseline assessments and offered Yakult or placebo (according to randomisation result) within 48 hours of commencing their antibiotic. The study drink will then be given once a day at the drug round in accordance with the protocol.

A master ID log will be maintained at each site.

The participant will be informed about their right to withdraw from the study at any time and for any reason without sanction, penalty, or loss of benefits to which the patient is otherwise entitled. A register will be kept of all patients who withdraw from the study. The reason for consent withdrawal will be documented along with the following core patient characteristics: age, gender and level and severity of spinal cord injury.

A copy of the signed Informed Consent Form - approved by the Research Ethics Committee - will be retained at the investigational site along with other investigational forms. A copy of the signed informed consent form will be placed into the patient's medical record, patient file (original) and a copy will be handed over to the patient.

### **5.4 Investigational product and comparator**

#### **5.4.1 Investigational product**

Yakult containing a minimum of  $6.5 \times 10^9$  live cells of *Lactobacillus casei* Shirota.

Subjects will receive one bottle of Yakult (a fermented milk drink containing the probiotic bacterium *Lactobacillus casei* Shirota) or an identical looking placebo, once daily during a

course of antibiotics and for 7 days after the course finishes after which participants will be followed for four weeks. The study intervention must be given within 48 hours of the patient commencing antibiotics.

Yakult and placebo will be supplied as fermented milk in sealed pots of 65 ml with date stamped expiry. They should be stored at approximately 7 degrees Celsius (domestic refrigerator). By the time of delivery, the products will have a shelf life of just over two weeks, so fresh supplies will be delivered every two weeks.

**Ingredients (Yakult):** Water, skimmed milk (reconstituted), glucose-fructose syrup, sugar, maltodextrin, flavouring, contains *Lactobacillus casei* Shirota.

| Nutritional Values | Per 100ml            | Per bottle (65 ml)   |
|--------------------|----------------------|----------------------|
| Energy             | 280.0 kJ / 66.0 kcal | 182.0 kJ / 42.9 kcal |
| Protein            | 1.3 g                | 0.9 g                |
| Carbohydrate       | 14.7 g               | 9.6 g                |
| Of which sugars    | 14.2 g               | 9.2 g                |
| Fat                | < 0.1 g              | < 0.1 g              |
| Of which saturates | < 0.1 g              | < 0.1 g              |
| Fibre              | 0 g                  | 0 g                  |
| Sodium             | 0.02 g               | 0.01 g               |

#### 5.4.2 Comparator

The placebo drink has similar packaging, taste and nutritional content, but does not contain any *L. casei* Shirota.

### 5.5 Study phases & Timeline

A schematic representation of the study phases & timeline is presented in [Appendix 1: Study flow chart](#).

#### 5.5.1 Recruitment & Informed Consent

See [headings 5.2 and 5.3](#) for details.

#### 5.5.2 Study procedure: opening assessments

After having obtained informed consent (1x copy to patients; 1x copy in medical notes; 1 x original in the investigator site file), basic patient's clinical characteristics and baseline measurements, as outlined on the Case Report Form (CRF, see [Item 12.1](#)), will be collected. No intervention will be administered prior to the completion of the study opening visit.

- Baseline demographics and clinical data
- Record use of medications (including use of antibiotics, laxatives, anti-diarrhoeal agents, proton pump inhibitors, H2 blocker)
- Nutrition risk scores – Spinal Nutrition Screening Tool (Wong et al, 2010, 2012)

- Quality of Life evaluation – WHO-QoL BREF ([http://www.who.int/substance\\_abuse/research\\_tools/en/english\\_whoqol.pdf](http://www.who.int/substance_abuse/research_tools/en/english_whoqol.pdf))
- Bowels function measures – stool type, duration of diarrhoea  
Definition of diarrhoea: two or more loose stools, Bristol Stool Scale (O'Donnell LD, 1990) type 5 or above.  
Constipation: using Rome III criteria: Functional constipation ([http://www.romecriteria.org/assets/pdf/19\\_RomeIII\\_apA\\_885-898.pdf](http://www.romecriteria.org/assets/pdf/19_RomeIII_apA_885-898.pdf)) (Drossman DA, 2006).
- Stool Specimen analysis (Kubota *et al.* 2014)  
One sample will be taken, frozen and stored frozen and then sent to YHER for TaqMan PCR analysis of toxigenic *C. difficile*. This analysis will be dependent on available resources at YHER. Further microbial analysis may also be done. This will be in the participant information sheet and on the consent form.

